### Data management

Data will be stored confidentially and anonymously on the research computer. Researchers obtaining patient data 30 days after study inclusion will work with decoded data. Afterwards, coding will be restored. All data will be held for 15 years after closure of the study. Handling of personal data will comply with the Dutch Personal Data Protection Act and the Belgian privacy legislation (http://wetten.overheid.nl/BWBR0011468/geldigheidsdatum_30-10-2013). Collected blood samples will be preserved for a maximum of 15 years. These samples will only be used for analyses that could contribute to our current field of research.

### Withdrawal or missing data

Should patients refuse informed consent after initial agreement on inclusion, they will be withdrawn from the study and their data abolished. If final diagnosis is impossible due to insufficient data, calculations will be made artificially regarding all patients with missing data as having an ACS, as well as regarding them as having no cardiac ischaemic cause for their initial complaints.

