Because of these diagnostic problems in primary care, most patients presenting complaints possibly matching ACS are still referred to a cardiologist [18]. A low threshold for referring patients with chest complaints to secondary care is an effective strategy for the GP to avert missed cases of ACS [19]. In the Netherlands, this strategy results in 78% of referred patients that are ACS negative in the emergency room (positive predictive value (PPV) is 22%), whereas ACS is present in 5% of patients that are not referred (negative predictive value (NPV) is 95%) and the outcome is probably not severely affected by initially not referring (specificity and sensitivity of clinical assessment by GP: 55%, resp 81%) [6,20]. To enhance triage by a GP and reduce patient burden in secondary care, new diagnostic tools should become available [21]. Combined with signs and symptoms, such tools should be able to safely rule out ACS in a significant number of otherwise referred patients, without a rise in missed cases of ACS. Importantly, this would lead to a significant cost reduction. The number of referred patients would decrease and in the remaining patients who are referred, ACS could be confirmed or ruled out as common in secondary care.

In the field of pulmonary embolism and respiratory tract infections, diagnostic tools combining clinical signs and symptoms with the result of a point of care (PoC) test have recently been introduced. Both increased efficiency by either reducing unnecessary referral (in cases of suspected pulmonary embolism) or treatment (in respiratory tract infections) [22-24]. For ACS, a similar procedure has not yet been defined.

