### Primary and secondary outcome

The most important feature of the algorithm of signs and symptoms combined with PoC H-FABP testing will be to adequately categorise all patients as either positive or negative for ACS. The ability of the algorithm to rule in UA in the ACS group is important, since UA is a condition that does not give a rise in biomarkers and diagnosis depends exclusively on signs and symptoms.

Primary outcome: using multivariate analysis of our data, signs and symptoms that have diagnostic value in an algorithm to predict or exclude ACS and AMI will be identified. The primary outcome measures of the study will be *s*ensitivity, specificity, positive and negative predictive value of an algorithm of those relevant signs and symptoms combined with PoC H-FABP testing for ACS and AMI, in patients with thoracic complaints of new onset in general practice. To determine influence of sex, age, duration of the complaints, and kidney function on clinical performance of H-FABP-testing, subgroup analyses within our study population will be performed [47,48].

Secondary outcome: an economic evaluation by means of an incremental cost-effectiveness ratio (ICER) will be performed. This evaluation will be performed by determination of the ratio between the difference in medical costs and the difference in benefits between the two strategies that are observed in this study, being the usual reference policy of the GP and the reference policy that could be created using a determined algorithm consisting of a clinical score and PoC H-FABP-testing. The benefits will be described as reduction in number of referred patients versus missed diagnoses if the algorithm is used.

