### Sample size and power calculation

An incidence of ACS of 22% would generate 132 patients with ACS and 468 patients without ACS in a study population of 600 patients. To create a usable algorithm consisting of signs, symptoms and H-FABP, the sensitivity of this algorithm should reach 85-90% and specificity should reach 80-85%. In a worst case scenario, where sensitivity would be 85% and specificity would be 80%, combined with the incidence of ACS of 22%, PPV of the algorithm of signs, symptoms and H-FABP for ACS would be 54% (95% C.I. 47-61%) and the NPV 95% (95% C.I. 93-97%). These diagnostic values with their 95% C.I. would be of significant interest, since PPV based on clinical judgment only is 22% and NPV is 95%. Therefore, a sample size of 600 generates adequate precision to find clinically relevant improvement of PPV, as compared to the current situation, and NPV that is at least not diminishing.

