### Statistical analyses

Receiver Operating Characteristic (ROC) curves have been used in an earlier stage to find the optimal cut-off point of the venous H-FABP-test [8]. Using 2 × 2 tables and multivariate analyses, including CART analysis, multiple logistic regression, or both, the diagnostic value of the H-FABP-test in combination with clinical findings for ACS and AMI will be assessed [49,50]. Our analysis will result in PPVs and NPVs, sensitivity and specificity and their 95% confidence intervals. Additionally, C-statistics will be presented to quantify overall prediction quality of the models.

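### Setting all missing diagnoses to ACS and then all to non-ACS bounds PPV and NPV, but not sensitivity or specificity; two crossed assignments are needed.

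*Protocol article*

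**What the plan says.** The protocol article, Withdrawal or missing data, gives a rule for a final diagnosis that cannot be made because data are insufficient: "calculations will be made artificially regarding all patients with missing data as having an ACS". A second calculation then takes the same patients the other way, "as well as regarding them as having no cardiac ischaemic cause for their initial complaints". The section does not say which calculation, if either, is the main one, and it gives no expected share of missing diagnoses.

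Under Primary and secondary outcome, the primary measures are sensitivity together with "specificity, positive and negative predictive value of an algorithm of those relevant signs and symptoms combined with PoC H-FABP testing for ACS and AMI". Statistical analyses adds: "Our analysis will result in PPVs and NPVs, sensitivity and specificity and their 95% confidence intervals". The algorithm is to come from multivariate analysis, "including CART analysis, multiple logistic regression, or both".

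Sample size and power calculation supplies the planning values: "An incidence of ACS of 22% would generate 132 patients with ACS and 468 patients without ACS in a study population of 600 patients", with a worst case of 85% sensitivity and 80% specificity.

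**The concern.** Setting every missing outcome one way and then the other looks like a worst-case and best-case pair. For a proportion whose denominator does not depend on the missing item, it is one. The denominators of PPV and NPV are the algorithm-positive and algorithm-negative patients, and these are known for everyone. The denominators of sensitivity and specificity are the patients with and without ACS, and these change with the assignment. For those two measures, one run of the pair always returns the complete-case value, so the pair shows movement in one direction only.

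The article describes safe exclusion of ACS as the GP's main task and sets a target of 85–90% for sensitivity. If the two results were read as the limits of what missing diagnoses could do, the possible movement in sensitivity and specificity would be understated.

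**Working it through.** **Plan's own figures.** From 600 patients with 132 ACS and 468 non-ACS: TP = 0.85 × 132 = 112.2, FN = 19.8, TN = 0.80 × 468 = 374.4, FP = 93.6. On rounded counts, PPV = 112/206 = 54.4% (exact 95% CI 47.3–61.3%; Wald 47.6–61.2%) and NPV = 374/394 = 94.9% (Wald 92.8–97.1%; exact 92.3–96.9%). The article's 54% (47–61%) and 95% (93–97%) agree within a percentage point, so the same 2 × 2 table is used below.

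**Formulas.** Let P and N be the complete patients with and without ACS, and let m+ and m− be the algorithm-positive and algorithm-negative patients without a diagnosis. The algorithm is held fixed.

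- All ACS: sensitivity (TP + m+)/(P + m+ + m−); specificity TN/N, unchanged.
- All non-ACS: sensitivity TP/P, unchanged; specificity (TN + m−)/(N + m+ + m−).
- Crossed, low (algorithm-negatives ACS, algorithm-positives non-ACS): sensitivity TP/(P + m−); specificity TN/(N + m+).
- Crossed, high (the reverse): sensitivity (TP + m+)/(P + m+); specificity (TN + m−)/(N + m−).

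Whenever m+ and m− are both above zero, the two planned values lie strictly inside the crossed ones.

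**Assumptions.** The missing share is taken as 2%, 5% or 10% of 600 (12, 30 or 60 patients). The algorithm-positive share of the missing is taken as that of the whole sample, 205.8/600 = 34.3%.

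**Example at 5%.** With 570 complete: P = 125.4, TP = 106.59, m+ = 10.29, m− = 19.71.

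- All ACS: 116.88/155.4 = 75.2%.
- All non-ACS: 106.59/125.4 = 85.0%.
- Crossed low: 106.59/145.11 = 73.5%.
- Crossed high: 116.88/135.69 = 86.1%.

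| Measure, share missing | All ACS | All non-ACS | Crossed low | Crossed high |
|---|---|---|---|---|
| Sensitivity, 2% | 80.7% | 85.0% | 80.1% | 85.5% |
| Sensitivity, 5% | 75.2% | 85.0% | 73.5% | 86.1% |
| Sensitivity, 10% | 68.0% | 85.0% | 63.8% | 87.2% |
| Specificity, 2% | 80.0% | 79.6% | 79.3% | 80.3% |
| Specificity, 5% | 80.0% | 79.1% | 78.2% | 80.8% |
| Specificity, 10% | 80.0% | 78.2% | 76.3% | 81.7% |

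**Coinciding specificities.** If the algorithm-positive share among the missing equals 1 − specificity, here 20%, both planned runs give 80.0%. At 10% missing (m+ = 12, m− = 48, N = 421.2, TN = 336.96), the all-non-ACS run is 384.96/481.2 = 80.0%. The real limits are 336.96/433.2 = 77.8% and 384.96/469.2 = 82.0%.

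**PPV and NPV.** At 5% missing, the planned pair gives PPV 51.8–56.8% and NPV 90.2–95.2%. The crossed assignments give the same end points, so the pair does bound these two.

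**Lower incidence.** The GP figures under Daily practice (PPV 22%, sensitivity 81%, specificity 55%) imply an incidence of 0.22 × 0.45/(0.81 × 0.78 + 0.22 × 0.45) = 0.099/0.7308 = 13.5%. With 30 missing, 25 of them algorithm-negative, the pair gives sensitivity 65.8–85.0% against 64.2–85.9%, and specificity 80.0–80.2% against 79.2–81.0%. The pattern does not depend on the 22%.

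**The case against.** The article does not claim that the pair bounds sensitivity or specificity, and does not say that the results will be presented as a range. The pair does bound PPV and NPV, the measures on which the sample size is justified. The shortfall is small when few diagnoses are missing, and it vanishes if all the missing are algorithm-negative. Sampling error is often larger: with 132 cases, a Wald interval around 85% sensitivity runs from 78.7% to 91.0%. All of this stands and limits the size of the point. It does not remove it, because sensitivity and specificity are named primary measures and the stated rule cannot show how far they could move.

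A reader might infer more than the text supports:

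- **That the trial has no usable main estimate, or handles missing diagnoses in no other way.** The article is condensed and any SAP is not shown. The two calculations may sit beside an observed-data analysis. With a fixed algorithm, they also contain the complete-case sensitivity and specificity.
- **That the two runs fall on either side of the 85% target.** Under these assumptions, one is at 85.0% and the other is below it.
- **That missing diagnoses will fall mainly in non-referred patients, so that the all-ACS run contradicts the statement that "ACS is present in 5% of patients that are not referred".** No section says where the missing diagnoses will arise. Non-referred patients are to have a troponin sample, and a 30-day enquiry and panel diagnosis are planned.
- **That the algorithm will be re-derived on each artificial outcome set, giving two algorithms.** The article speaks only of calculations.

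**Conclusion.** The concern holds in a limited form. For a fixed algorithm, the stated pair bounds PPV and NPV but not sensitivity or specificity whenever both algorithm-positive and algorithm-negative diagnoses are missing. That is algebra and needs no assumption about the missing share.

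The size does depend on assumptions: 22% ACS, 85% and 80% accuracy in complete cases, and 34% of the missing algorithm-positive. For sensitivity, the pair falls short of the real limits as follows:

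- 2% missing: about 0.5 points at each end.
- 5% missing: 1.7 points at the lower end and 1.1 at the upper.
- 10% missing: 4.2 points at the lower end and 2.2 at the upper.

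The most misleading case is specificity, where the two runs can agree exactly while the real limits lie about four points apart. This is a correctable weakness in a stated rule. It does not show that the primary analysis is unusable.

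**What to change.** Amend Withdrawal or missing data, or the analysis plan, as follows.

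1. Call the all-ACS and all-non-ACS runs sensitivity analyses. Hold the algorithm fixed, as derived from patients with a panel diagnosis.
2. Add the two crossed assignments: algorithm-negatives as ACS with algorithm-positives as non-ACS, and the reverse. Report these as the limits for sensitivity and specificity, and the two existing runs as the limits for PPV and NPV.
3. State that neither extreme run is the main estimate, and name the one that is. Either complete-case analysis or multiple imputation from data already collected (signs and symptoms, H-FABP result, GP diagnosis and referral decision, troponin) would be acceptable, with its assumption stated. The point does not depend on which is chosen.
4. Report the number of missing diagnoses by algorithm result.

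The cost is a few sentences and a little programming, with no new data. The downside is slightly wider reported ranges for sensitivity and specificity.

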### Sample size and power calculation

An incidence of ACS of 22% would generate 132 patients with ACS and 468 patients without ACS in a study population of 600 patients. To create a usable algorithm consisting of signs, symptoms and H-FABP, the sensitivity of this algorithm should reach 85-90% and specificity should reach 80-85%. In a worst case scenario, where sensitivity would be 85% and specificity would be 80%, combined with the incidence of ACS of 22%, PPV of the algorithm of signs, symptoms and H-FABP for ACS would be 54% (95% C.I. 47-61%) and the NPV 95% (95% C.I. 93-97%). These diagnostic values with their 95% C.I. would be of significant interest, since PPV based on clinical judgment only is 22% and NPV is 95%. Therefore, a sample size of 600 generates adequate precision to find clinically relevant improvement of PPV, as compared to the current situation, and NPV that is at least not diminishing.

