## Background

### Daily practice

Patients presenting with chest complaints caused by acute coronary syndrome (ACS) need urgent transport to a specialist setting [1,2]. In these situations, favourable outcome is inversely related to the time interval between onset of complaints and vascular rescue treatment. However, in daily practice, most patients experiencing chest complaints primarily apply to a general practitioner (GP). Within this population, benign conditions such as thoracic wall complaints, gastric disease or psychiatric and somatoform disease, largely outnumber cases of ACS [3-5]. In specialised care facilities such as coronary care units, 50% of patients presenting with chest pain are diagnosed with ACS, whereas in primary care, ACS is diagnosed in no more than 1.5-22% of cases [6-8]. Referring every patient with chest complaints would overwhelm secondary care facilities, however the GP is faced with serious diagnostic dilemmas since milder diseases with beneficial outcome can mimic ACS and vice versa [9]. Safe exclusion, rather than inclusion, is the main task of a GP in assessing chest complaints.

In primary care, where clearly circumscribed diseases with specific symptoms are embedded in a broad scope of illness and mild disease with less typical appearance, discriminative signs are usually scarce. This applies in particular to ACS, where history, physical examination and electrocardiography notoriously lack sensitivity and specificity as has been extensively surveyed [10-12]. With regard to chest pain, only few signs and symptoms, for example, the absence of pain on chest palpation or presence of pain on exertion, generate discriminative strength in diagnostic studies, although to a limited extent [9,13,14]. Altogether, clinical signs and symptoms are inappropriate for ruling out ACS or lack additive value above the clinical judgment by the GP, which on itself is correct in a majority of cases [6]. Weighing more abstract factors (e.g. contextual patient factors and altered presentation in time) probably leads to this fairly adequate clinical judgment of GPs [15-17].

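### The sample-size paragraph sets algorithm PPV and NPV computed at 22% ACS prevalence against GP values that hold only at about 13.5%, so the PPV gain is overstated and an NPV gain is hidden

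*Protocol article*

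**What the plan says.** The Protocol article, under Sample size and power calculation, opens with this statement: "An incidence of ACS of 22% would generate 132 patients with ACS and 468 patients without ACS in a study population of 600 patients". The paragraph continues: "In a worst case scenario, where sensitivity would be 85% and specificity would be 80%, combined with the incidence of ACS of 22" per cent, the PPV "would be 54% (95% C.I. 47-61%) and the NPV 95% (95% C.I. 93-97" per cent). It calls these values of interest "since PPV based on clinical judgment only is 22% and NPV is 95" per cent, and concludes that 600 patients give adequate precision to show a better PPV and an NPV that does not fall.

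The GP comparators come from Daily practice in the Background. For referred patients, "this strategy results in 78% of referred patients that are ACS negative in the emergency room (positive predictive value (PPV) is 22" per cent). For the others, "ACS is present in 5% of patients that are not referred (negative predictive value (NPV) is 95" per cent). The same sentence adds "specificity and sensitivity of clinical assessment by GP: 55%, resp 81" per cent. Earlier in that section the range is given: "in primary care, ACS is diagnosed in no more than 1.5-22% of cases". The Abstract repeats the range, and the section on biomarkers and point of care testing works with an incidence of 20% or less.

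The study enrols patients whether or not they are referred. Inclusion depends on the GP considering a cardiac origin possible, and Data collection arranges a venous sample for those who are not referred.

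**The concern.** PPV and NPV depend on prevalence, so two strategies can be compared on them only at the same prevalence. The paragraph uses 22% in two roles: as the ACS prevalence in all 600 patients and as the PPV of GP judgment. With 22% ACS among referred and 5% among non-referred patients, the overall prevalence is a weighted average of the two. It reaches 22% only if everyone is referred, and the stated GP sensitivity and specificity rule that out.

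This comparison is the article's only justification of the sample size. Two things are at stake: the size of the claimed improvement over current care, and the number of ACS cases available to derive the algorithm and estimate its sensitivity.

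**Working it through.** **Inputs.** N = 600, prevalence 22%, algorithm sensitivity 85% and specificity 80%, comparator PPV 22% and NPV 95% (Sample size and power calculation). GP sensitivity 81%, specificity 55%, PPV 22%, NPV 95%; primary-care range 1.5-22% (Daily practice).

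**Formulas.** With prevalence p, sensitivity se and specificity sp:

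- PPV = se·p / [se·p + (1−sp)(1−p)]
- NPV = sp(1−p) / [sp(1−p) + (1−se)p]
- 95% CI: estimate ± 1.96·√(q(1−q)/n), with q the estimated proportion and n the expected number of test positives, test negatives or ACS cases

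**Step 1: the plan's own figures.** 600 × 0.22 = 132 ACS and 468 non-ACS.

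- TP = 132 × 0.85 = 112.2; FP = 468 × 0.20 = 93.6; PPV = 112.2/205.8 = 54.5% (47.7-61.3%).
- TN = 468 × 0.80 = 374.4; FN = 132 × 0.15 = 19.8; NPV = 374.4/394.2 = 95.0% (92.8-97.1%).

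Up to rounding and choice of interval, these match the stated 54% (47-61%) and 95% (93-97%). The arithmetic at 22% is sound.

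**Step 2: the prevalence at which the GP figures hold.** Inverting the formulas:

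- From PPV: p = 0.22 × 0.45 / (0.22 × 0.45 + 0.81 × 0.78) = 13.5%. Allowing for rounding of the inputs: 13.0-14.1%.
- From NPV: p = 0.55 × 0.05 / (0.55 × 0.05 + 0.19 × 0.95) = 13.2%. Allowing for rounding: 11.6-14.9%.

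The four GP figures agree with each other near 13.5%, and rounding cannot stretch that to 22%. At 13.5% the share referred is 0.135 × 0.81 + 0.865 × 0.45 = 50%.

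**Step 3: the GP at 22%.** TP = 132 × 0.81 = 106.9; FP = 468 × 0.45 = 210.6; PPV = 106.9/317.5 = 33.7%. TN = 257.4; FN = 25.1; NPV = 257.4/282.5 = 91.1%. These, not 22% and 95%, are the comparators that belong beside 54% and 95%.

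**Step 4: the algorithm at 13.5%.** 81 ACS and 519 non-ACS. TP = 68.9; FP = 103.8; PPV = 68.9/172.7 = 39.9% (33-47%). TN = 415.2; FN = 12.2; NPV = 415.2/427.4 = 97.2% (96-99%).

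**Step 5: the comparison, with each side at one prevalence.**

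| Basis | PPV, rule vs GP | Gain (points) | NPV, rule vs GP | Gain (points) |
|---|---|---|---|---|
| As stated (mixed) | 54% vs 22% | 32 | 95% vs 95% | 0 |
| 22% for both | 54.5% vs 33.7% | 21 | 95.0% vs 91.1% | 3.9 |
| 13.5% for both | 39.9% vs 21.9% | 18 | 97.2% vs 94.9% | 2.3 |

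**Step 6: across the range.**

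| Prevalence | ACS cases | Rule PPV (95% CI) | GP PPV | Rule NPV (95% CI) | GP NPV | 95% CI for 85% sensitivity |
|---|---|---|---|---|---|---|
| 5% | 30 | 18.3% (11.9-24.7) | 8.7% | 99.0% (98.1-99.9) | 98.2% | 72-98% |
| 10% | 60 | 32.1% (24.8-39.3) | 16.7% | 98.0% (96.6-99.3) | 96.3% | 76-94% |
| 13.5% | 81 | 39.9% (32.6-47.2) | 21.9% | 97.2% (95.6-98.7) | 94.9% | 77-93% |
| 22% | 132 | 54.5% (47.7-61.3) | 33.7% | 95.0% (92.8-97.1) | 91.1% | 79-91% |

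The half-width for sensitivity is 1.96·√(0.85 × 0.15/132) = 6.1 points with 132 cases and 1.96·√(0.85 × 0.15/81) = 7.8 points with 81.

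**The case against.** The strongest defence is that the conclusion does not depend on the error. A rule at 85%/80% beats a GP at 81%/55% on both measures: the positive likelihood ratio is 0.85/0.20 = 4.25 against 0.81/0.45 = 1.80, and the negative one is 0.15/0.80 = 0.19 against 0.19/0.55 = 0.35. Its PPV and NPV are therefore better at every prevalence. Precision for PPV and NPV also hardly changes between 22% and 13.5%: half-widths go from 6.8 to 7.3 points for PPV and from 2.1 to 1.6 for NPV. All of this stands.

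Four stronger readings are tempting, and the article does not support them:

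- **That 22% is only the rate in referred patients.** It is that, but the Abstract and Daily practice also give it as the upper end of a primary-care range. As a planning value it is optimistic for the case count, not without basis.
- **That the worst-case label is plainly wrong.** It attaches most naturally to the low ends of the sensitivity and specificity targets in the preceding sentence. Moreover, 22% is the least favourable value in the range for NPV, and Daily practice names safe exclusion as the GP's main task. The wording is merely open to misreading, because 22% is the most favourable value for PPV and case count.
- **That at 5% prevalence the rule does worse than current care, because its PPV of 18% is below 22%.** That comparison also mixes prevalences: the GP's PPV at 5% is 8.7%.
- **That the study will have 81 ACS cases.** The 13.5% is worked back from rounded figures for an earlier GP population. This study has its own entry criteria, such as complaints of at most 24 hours, and its prevalence cannot be settled from the article.

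**Conclusion.** The point holds as a mismatch of prevalence in the comparison, not as a slip in arithmetic. Whichever prevalence is chosen, one side of the stated comparison is wrong: at 22% the GP comparators should be about 34% and 91%, and at 13.5% the algorithm's values should be about 40% and 97%. The PPV gain is 18 to 21 points rather than 32, and the apparent tie on NPV hides a gain of about 2 to 4 points. The count of 132 ACS cases sits at the optimistic end of the article's range; 81 is the scenario that its GP figures imply, 38% fewer (51/132), with a somewhat wider interval for sensitivity.

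This rests on the stated GP sensitivity and specificity and, for the 13.5% figures only, on that population resembling the one enrolled. The inconsistency itself does not need that second assumption. The direction of the conclusion is unaffected, and nothing here shows that 600 patients is too few for the paragraph's stated aim.

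**What to change.** Rewrite the sample-size paragraph as follows:

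- Use one prevalence for both the algorithm and the GP. Either take 13.5% throughout (81 ACS and 519 non-ACS; PPV 40%, 33-47%, against 22%; NPV 97%, 96-99%, against 95%), or keep 22% and replace the comparators with PPV 34% and NPV 91%.
- Show ACS count, PPV, NPV and the CI for sensitivity over a prevalence range, for example 5%, 10%, 13.5% and 22%, with the GP values recomputed at each.
- State that worst case refers to the assumed sensitivity and specificity, not to the prevalence.
- If 13.5% is used, say that it is derived from the GP figures in Daily practice and assumes that they carry over.

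The cost is one reworded paragraph and a less favourable stated PPV gain. Design and sample size stay as they are, and no extra patients are needed.

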When H-FABP-testing is combined with signs and symptoms in a *diagnostic algorithm*, NPV hypothetically improves and thus the number of patients that are referred by a GP but turn out to have no ACS, could be reduced. Even with a moderate amount of false positive results, such an algorithm could improve daily practice since currently, the majority of patients without underlying ACS are referred to secondary care facilities. Thus, our hypothesis is that net reduction of referral rate – without an increase in missed cases of ACS – in patients presenting chest complaints to their GP could be accomplished by the aforementioned algorithm including PoC H-FABP-testing. Therefore a PoC H-FABP-device meeting the demand of a lower cut-off value of 4 ng/ml has recently been developed by FABPulous B.V. We intend to study the diagnostic value of this device in primary care. The methodology of the study is presented in the remainder of this article in order to inform colleagues in the same research field, to anticipate forthcoming results of our study and to prevent publication bias or violation of the protocol during the running time of the study.

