### Study design and objectives

This current study is a derivation study to identify signs and symptoms that, combined with point of care heart-type fatty acid-binding protein (PoC H-FABP) testing, can be part of an algorithm to confirm or rule out ACS (meaning AMI and unstable angina (UA)) and AMI alone in a population of patients with complaints possibly due to myocardial ischaemia in general practice. Thus, stage 2 of the 6 major stages in the development and testing of a clinical decision rule as defined by Stiell and Wells will be studied [42]. The diagnostic value of the algorithm will be studied and compared to regular assessment by a GP without PoC H-FABP testing using a delayed type cross-sectional diagnostic model. Both ACS and AMI as a subgroup of ACS will be analysed as final diagnosis. The cost-effectiveness of the test will also be evaluated. The study commenced in November 2013 and will run for two years. External validation of the algorithm derived from this study needs to be performed in future studies.

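### The sample-size section claims adequate precision for an undiminished NPV, but its own interval does not support this, and NPV is the wrong scale for missed ACS

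*Protocol article*

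**What the plan says.** The hypothesis, at the end of the Background section on biomarkers and point of care testing, is a net reduction in referrals "without an increase in missed cases of ACS". Under Study design and objectives, the algorithm is to be "compared to regular assessment by a GP without PoC H-FABP testing".

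The Sample size and power calculation section assumes an ACS incidence of 22%, which "would generate 132 patients with ACS and 468 patients without ACS in a study population of 600 patients". It sets a target: "the sensitivity of this algorithm should reach 85-90% and specificity should reach 80-85" (per cent). At the lower corner of that target it projects a PPV of 54% (47-61%) "and the NPV 95% (95% C.I. 93-97" (per cent). It compares these with a PPV of 22% and an NPV of 95% for clinical judgment alone. From this it concludes that 600 patients are enough to find "clinically relevant improvement of PPV, as compared to the current situation, and NPV that is at least not diminishing". It gives no margin for NPV and no interval for sensitivity.

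The comparator values come from the Background section on daily practice, which gives GP sensitivity 81%, specificity 55%, PPV 22% and NPV 95%. Under Data collection, the GP's referral decision is written down before the test result is read.

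**The concern.** The adequacy statement is the section's only safety argument for 600 patients, and it has three weaknesses.

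- The projected NPV and its comparator are the same number, so an interval around it must extend below the comparator. Without a margin, such an interval cannot show that NPV has not fallen.
- The hypothesis is about missed cases. Missed cases equal (1 − NPV) times the number of patients not referred. The algorithm is meant to enlarge that number, so an unchanged NPV then goes with more missed ACS. Within the same patients, no increase in missed ACS means a sensitivity no lower than the GP's.
- The 95% is a fixed value from outside the study, set beside a projection made at an incidence at which the GP figures do not produce 95%.

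At stake is whether a report could cite an NPV near 95% from 600 patients as evidence of safety when the comparison of missed cases remains imprecise.

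**Working it through.** **Inputs.** From Sample size and power calculation: N = 600, 132 ACS, 468 non-ACS, algorithm sensitivity 85% and specificity 80%, comparator NPV 95%. From Daily practice: GP sensitivity 81%, specificity 55%, PPV 22%, NPV 95%. The discordance values in step 6 are assumptions.

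**1. Reproduce the plan's figures.** TP = 0.85 × 132 = 112.2; FN = 19.8; TN = 0.80 × 468 = 374.4; FP = 93.6.
- PPV = 112.2/205.8 = 54.5% (Wald 47.7-61.3%).
- NPV = 374.4/394.2 = 94.98%; half-width 1.96 × √(0.9498 × 0.0502/394.2) = 2.2 points, giving 92.8-97.1%.

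The printed figures match within rounding.

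**2. Set the interval against the 95% benchmark.** With 394 negatives, the Wald lower limit reaches 95% only if observed NPV is at least 382/394 = 97.0%. Of the four corners of the target range, only 90%/85% achieves this (NPV 96.8%, Wald 95.1-98.5%), and its Clopper-Pearson lower limit is 94.6%. The printed lower limit also matters on the missed-case scale. NPV 93% at specificity 80% means FN = 374.4 × 0.07/0.93 = 28.2, a sensitivity of 1 − 28.2/132 = 79%. The GP at 81% misses 0.19 × 132 = 25.1.

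**3. NPV against missed cases.** Equal NPV means an equal ratio FN/TN. Missed cases therefore scale with specificity, whatever the prevalence: 0.80/0.55 = 1.45. At equal NPV and specificity 80%, sensitivity would be 1 − 0.19 × 1.45 = 72%, against the GP's 81%.

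**4. Does the benchmark fit the assumed incidence?** At 22% ACS the GP has TN = 0.55 × 468 = 257.4 and FN = 25.1, so NPV = 257.4/282.5 = 91.1%. PPV is 106.9/(106.9 + 210.6) = 33.7%. Solving for the ACS proportion that reproduces the quoted GP values gives 13.5% from PPV 22% and 13.2% from NPV 95%. At 13.5%, 600 patients contain 81 ACS cases.

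**5. Precision of sensitivity on its own.** Half-width = 1.96 × √(0.85 × 0.15/n).
- n = 132: ±6.1 points, 79-91%.
- n = 81: ±7.8 points, 77-93%.

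Both include 81%.

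**6. Precision of the paired difference.** Half-width = 1.96 × √((d − δ²)/n), with δ = 0.85 − 0.81 = 0.04 and d the share of ACS patients in whom algorithm and GP disagree.

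| d | 132 ACS | 81 ACS |
|---|---|---|
| 15% | ±6.6 | ±8.4 |
| 20% | ±7.6 | ±9.7 |
| 25% | ±8.5 | ±10.9 |

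The documents do not give d. It cannot be below 4% (the difference itself); independent decisions would give 0.85 × 0.19 + 0.15 × 0.81 = 28%. With 132 cases the interval around +4 points runs from 0.7 to 7.3 at d = 4%, but already from −1.4 to 9.4 at d = 10%.

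**The case against.** A reader might infer that the plan would accept a rule that misses more ACS than GPs do now, or that the algorithm is expected to do so. The documents do not support this. The same section asks for a sensitivity of 85-90%, above the GP's 81%. A rule that truly reached 85% would miss 19.8 against 25.1 of 132 cases. The 72% in step 3 shows what NPV alone would let through; the protocol would not call such a rule usable.

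The NPV sentence is also not a formal decision rule. It is a precision argument in a derivation study that leaves external validation to later work. Sensitivity is among the primary outcome measures, intervals are promised under Statistical analyses, and comparison with GP assessment is an objective. The use of a fixed external comparator is therefore a fault of the sample-size paragraph, not of the whole design.

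Finally, much of the overlap with 95% comes from mixing incidences. At 22%, the projected 93-97% lies above the GP's 91.1%. At 13.5%, sensitivity 85% and specificity 80% give NPV = 415.2/(415.2 + 12.15) = 97.2% (Wald 95.6-98.7%), above 95%. This stands as a reason not to read the overlap as a sign of a poor algorithm. It does not rescue the printed claim, which uses 22% for one side and 95% for the other. Nor does it establish safety, since it treats the GP value as known without error and stays on the NPV scale.

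**Conclusion.** The concern holds as a fault in the sample-size argument. The printed interval does not support adequate precision for an undiminished NPV. NPV does not measure the quantity in the hypothesis. The benchmark and the projection rest on different ACS proportions (about 13.5% and 22%).

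The 85-90% sensitivity target points the right way, but the section gives it no precision. An expected advantage of 4 points over the GP is smaller than the paired half-width of about 7 to 9 points (132 cases) or 8 to 11 points (81 cases). Unless algorithm and GP disagree in very few ACS patients, 600 patients cannot by themselves establish that missed ACS does not increase.

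These half-widths assume 15-25% discordance and the projected 85% and 81%. They make no allowance for the optimism of testing a rule on the data that produced it. The finding says nothing about whether the algorithm will in fact miss more cases. The PPV half of the sentence is not in dispute: at 22% ACS the projected 54% (47-61%) still exceeds the GP's 34%.

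**What to change.** - Replace the sentence on undiminished NPV with the precision that 600 patients give for the within-patient difference in sensitivity, algorithm minus recorded pre-test GP decision. State it for 132 and for 81 ACS cases, with the assumed discordance.
- Name the paired differences in sensitivity (safety) and specificity (referrals avoided), each with a 95% CI, as the main comparisons. Keep PPV and NPV as descriptive measures.
- Use one ACS proportion for both algorithm and comparator.
- If a claim of no increase in missed ACS is to be kept, state and justify a margin for the sensitivity difference.
- Do not set the algorithm's cut-off by matching the GP's observed sensitivity in the same data; that would make the later comparison partly true by construction.

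The cost is rewording the sample-size and analysis paragraphs, because the GP's decision is already recorded for each patient. The downside is that the stated safety claim becomes weaker.
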